This study is designed as a pilot study to evaluate the physiologic efficacy (rather than effect on clinical outcomes) of NO administered by hood in improving oxygenation of neonates with elevated alveolar - arterial oxygen gradients (A-a DO2). If this is shown to be achievable, subsequent larger trials can determine if this method of NO administration can decrease the need for mechanical ventilation, ECMO, or other major outcomes.

1.1 Primary outcome measure:

Partial pressure of oxygen in post-ductal arterial blood (PaO2)

1.2 Secondary outcome measures:

1. Alveolar-arterial oxygen gradient (A-a DO2) after one hour of exposure to treatment gas
2. Alveolar-arterial oxygen ratio (A/a O2)
3. Oxygen saturation by pulse oximetry (SpO2)
4. Need for mechanical ventilation
5. Duration of oxygen therapy
6. Methemoglobin level in post-ductal arterial blood (MetHb)*
7. Platelet count*
8. Systemic blood pressure*
9. Environmental NO and NO2 exposure*

(* Safety indicators)

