1.3 Hypotheses

The primary hypothesis is that administration of nitric oxide gas by oxygen hood at 20 ppm to neonates with elevated A-a DO2 (500-600 mmHg) significantly increases PaO2, as compared to placebo gas (oxygen), within one hour of initiation, and with no significant adverse effects.

Secondary hypotheses

1. Administration of nitric oxide decreases A-a DO2as compared to placebo gas (oxygen)
2. Administration of nitric oxide decreases A/a O2 as compared to placebo gas (oxygen)
3. Administration of nitric oxide increases SpO2 as compared to placebo gas (oxygen)
4. Administration of nitric oxide decreases the need for mechanical ventilation as compared to placebo gas (oxygen)
5. Administration of nitric oxide at 20 ppm by oxygen hood does not increase duration of oxygen therapy significantly as compared to placebo gas (oxygen)
6. Administration of nitric oxide at 20 ppm by oxygen hood does not increase MetHb significantly as compared to placebo gas (oxygen)
7. Administration of nitric oxide at 20 ppm by oxygen hood does not decrease platelet counts significantly as compared to placebo gas (oxygen)
8. Administration of nitric oxide at 20 ppm by oxygen hood does not decrease mean systemic blood pressure significantly as compared to placebo gas (oxygen)
9. Administration of nitric oxide at 20 ppm by oxygen hood does not increase environmental NO and NO2 significantly as compared to placebo gas (oxygen)

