3.4 Apparatus, protocols, and monitoring

Apparatus:

We have developed a "double-hood" model for the administration of NO via oxygen hood. The oxygen/NO/N2 blend is administered to inner hood and
suctioned out of outer hood (and inner hood via NO/NO2 sensors). The inner hood is made of Plexiglas (Olympic oxyhood; 10 inch diameter) and the outer hood is made of plastic sheeting (NOVA tenthouse oxygen tent; 12 x 12 x 10 inch).

100% oxygen (15 lpm) is blended with a NO/nitrogen mixture (800 ppm NO; balance N2) to yield a final concentration of 24 ppm NO, NO2 0.25 ppm, 97 % oxygen, 3 % nitrogen. This becomes the flow into the inner hood, from which the neonate breathes.

A suction apparatus is attached to the outer hood which suctions the gases in the outer hood at approximately 4 lpm. The NO/NO2 sensor lead in the inner hood also suctions approximately 4 lpm. Both suction systems are attached to a vented connector attached to the wall suction which entrains room air and is regulated to a negative pressure of –9 to –10 cm H20.

The concentration of NO in the inner hood with this apparatus is approximately 20 ppm, with NO2 0.95 ppm, and 97 % oxygen. The concentrations in the outer hood are: NO 15-17 ppm, with NO2 0.60-1.05 ppm, and 65-77 % oxygen.

On the outer surface of the hood, near the opening, the concentrations of NO are 0.45-0.55 ppm, with NO2 0.00 ppm, and 22-35 % oxygen. Further away from the hood, the oxygen concentration is 21% (same as room air) and NO2 is undetectable (0.00 ppm). NO levels are < 0.25 ppm at more than 12 inches (30 cm) from the hood.

Protocols:

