After entry criteria are met, informed consent is obtained from the parents by either the study coordinator, research nurse, or attending physician/fellow and the neonate will be randomized to either the NO group or control group. The treatment gas will be administered by hood, with the clinicians and nurses blinded to assignment. The apparatus setup at the bedside would be identical for both groups and the NO flowmeter and NO/NO2 concentrations will be masked. FiO2 and NO/NO2 concentrations of the inflow gas will be monitored at the beginning of the study period and the sensors will then be moved to the inner hood. Respiratory therapists will adjust flow and blending to administer 20 ppm of NO or an equivalent flow of O2. FiO2 and NO/NO2 concentrations in the inner hood will be monitored continuously for the study period. Physicians and nurses caring for the patient and analyzing results will be blinded to patient assignment. After completion of one hour on the study, the gas will be weaned every hour over the next four hours (20 ppm at 1 hour to 10 ppm at 2 hours to 5 ppm at 3 hours to 2.5 ppm to 4 hours to 0 ppm at 5 hours), then discontinued. If marked deterioration (decrease in oxygen saturation of > 5%) is seen during the weaning phase, the treatment gas can be increased to the previous level and can then be weaned subsequently by the same decrement but over two hours. The attending physician can initiate mechanical ventilation at any point during this study, based on clinical or other grounds. If methemoglobinemia (MetHb>5%) occurs, or if NO2 concentrations are >3% in the inner hood, or if oxygenation decreases significantly (decrease in oxygen saturation of > 5%), or if other adverse reactions that could possibly be related temporally to the treatment gas are evident, the gas is to be weaned in a shorter timespan (50% every 15 minutes). The results of these neonates will still be analyzed based on "intention to treat". If at the end of the study period the infant still meets entry criteria, he/she will be crossed over into the other treatment group.

Monitoring:

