1. Apparatus: FiO2 and NO/NO2 concentrations will be checked in the **inflow gas** at the beginning, and continuous monitoring of FiO2 and NO/NO2 concentrations in the **inner hood** will be done till exit from study. FiO2 and NO/NO2 concentrations will also be measured **outside the hood** 30 min and one hour after commencement of the treatment, at a distance of one foot (30 cm) from the front of the hood.
2. Baby: **ABGs** at 0 hours (the last ABG before beginning treatment gas) and 1 hour will be used for the study. **MetHb** will also be measured in these samples. Frequency of ABG and other lab investigations at other times will be at the discretion of the attending physician, but should be at least q 1 hour for the five hours on the study. **Oxygen saturation, heart rate, respiratory rate** and **blood pressures** (by arterial catheter) will be monitored continuously through the period of study. A **platelet count** obtained less than 12 hours before entry into the study will also be compared with one obtained immediately after completion of one hour of exposure to the treatment gas. **Echocardiograms** are encouraged before entry into the study, as echocardiograms are usually part of the clinical investigation in neonates with suspected PPHN, but are not a pre-requisite for entry in view of time and technical constraints.

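### Secondary hypothesis 9 tests environmental NO and NO2 against an arm with no NO source and sets no room-air limit, so neither result shows whether exposure is acceptable

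*Protocol*

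**What the plan says.** Section 1.2 lists "Environmental NO and NO2 exposure" as the ninth secondary outcome and stars it as a safety indicator. The matching hypothesis in section 1.3 is that NO at 20 ppm by hood "does not increase environmental NO and NO2 significantly as compared to placebo gas (oxygen".

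On the two gases, section 3.4 (Protocols) says: "Respiratory therapists will adjust flow and blending to administer 20 ppm of NO or an equivalent flow of O2". The control arm thus receives oxygen in place of the NO blend.

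Section 3.4 (Apparatus) reports bench measurements with NO running:

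- At the hood: "On the outer surface of the hood, near the opening, the concentrations of NO are 0.45-0.55 ppm, with NO2 0.00 ppm".
- Further away: "NO2 is undetectable (0.00 ppm".
- For NO at a distance: "NO levels are < 0.25 ppm at more than 12 inches (30 cm) from the hood".

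Section 3.4 (Monitoring, item 1) places the trial's readings outside the hood "at a distance of one foot (30 cm) from the front of the hood", at 30 minutes and at one hour. Section 3.9 names repeated measures ANOVA, the unpaired t-test or non-parametric alternatives, with 20 infants per group.

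**The concern.** A safety outcome of this kind asks whether people near the hood breathe an acceptable concentration. That needs a limit. Hypothesis 9 offers only the word *significantly* and a comparator whose readings can be nothing but room background.

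The protocol supplies no limit elsewhere. The methemoglobin and NO2 triggers in sections 3.4 and 3.7 concern the infant and the inner hood. Section 2.2 describes the environmental levels in a cited case report (NO below 0.06 ppm, NO2 below 0.3 ppm) as within safety margins, but it neither gives those margins as figures nor adopts them for this trial.

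Both outcomes of the test can therefore mislead. A small, steady and harmless leak could fail the hypothesis. A larger but erratic leak could pass it, because a non-significant difference test is not evidence of acceptable exposure. For a pilot of a new delivery apparatus, this is the safety question that the next trial would inherit unanswered.

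**Working it through.** **1. The plan's own figure.** The protocol gives no power for hypothesis 9. Its stated power is for PaO2: 85% with 20 per group, alpha 0.05, a difference of 25% and an SD of 25% of the mean, so d = 0.25/0.25 = 1.0. A two-sided two-sample t-test gives 0.869, close to the stated figure. It has no bearing on hypothesis 9 except to show that 20 per group was chosen for another outcome.

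**2. Method for hypothesis 9.** I used the same test: two-sided alpha 0.05, n = 20 per group, 38 degrees of freedom, d = (NO-arm mean − oxygen-arm mean)/SD, noncentrality d × √(20/2) = 3.16 d. The smallest difference detectable with 80%, 85% and 90% power is 0.91, 0.97 and 1.05 SD.

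**3. Assumptions.** The oxygen-arm background is 0 ppm. The mean level at 30 cm and the SD are not in the protocol, so I took ranges. The SD is the same in both arms.

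| Assumed NO rise at 30 cm (ppm) | SD 0.02 | SD 0.05 | SD 0.10 | SD 0.15 | SD 0.25 |
|---|---|---|---|---|---|
| 0.02 | 0.87 | 0.23 | 0.095 | 0.07 | 0.06 |
| 0.05 | >0.99 | 0.87 | 0.34 | 0.18 | 0.095 |
| 0.20 | >0.99 | >0.99 | >0.99 | 0.98 | 0.69 |

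Entries are the probability of a significant result. Worked example: a rise of 0.05 ppm with SD 0.10 gives d = 0.5, noncentrality 1.58 and probability 0.34.

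A rise of 0.02 ppm with SD 0.02 (0.87) is more likely to fail the hypothesis than a rise ten times as large with SD 0.25 (0.69). The result follows the ratio of level to scatter, not the level.

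**4. How far the table can be pressed.** If every reading lay between 0 and the bench bound of 0.25 ppm, the SD at a mean of 0.05 could not exceed √(0.05 × 0.20) = 0.10. The SD 0.25 column therefore requires some bedside readings above the bench bound, which is the case a safety measure should catch. If all the scatter sat in the NO arm, the pooled SD would be SD/√2. For a rise of 0.05 ppm, the probabilities at SD 0.10 and 0.25 would then be about 0.59 and 0.14. For a rise of 0.20 ppm at SD 0.25, the probability would be about 0.94. The ranges narrow, but the dependence on scatter remains.

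**5. NO2.** The bench value outside the hood is 0.00 ppm. If that holds at the bedside, the expected difference is 0 and the chance of a significant result is at most about 5%.

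**6. Bench data against the measuring point.**

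| Place | NO | NO2 | Measured during the trial? |
|---|---|---|---|
| Outer surface, near opening | 0.45–0.55 ppm | 0.00 ppm | No |
| More than 30 cm away | below 0.25 ppm (bound only) | undetectable | Yes, at 30 cm |

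No oxygen-only background reading is given for either place.

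**The case against.** The strongest defence is that the outcome is recorded in ppm, so anyone can read the values against an occupational or institutional limit whatever the test says, and that an analysis plan may name one. It is also the last of nine secondary hypotheses in a pilot of 40 infants, and no exit criterion or sample size depends on it. All of this is true, and it keeps the point away from the primary result. It does not rescue the hypothesis: the protocol itself fixes the comparator and the criterion, and that criterion cannot answer the safety question.

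A reader might go further and infer that the bench data already contradict hypothesis 9, or that it will most likely fail. The documents do not support either reading. Bench NO2 outside the hood agrees with the hypothesis. The clear NO elevation is at the opening, not at the trial's measuring point, where the only figure is an upper bound compatible with a value near zero. One can show a Mann-Whitney p of about 8 × 10⁻⁹ with 20 oxygen readings at zero and 20 NO readings between 0.05 and 0.25 ppm, but that assumes complete separation of the arms rather than deriving it.

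Nor does the stated flow balance prove a rise at 30 cm. It leaves roughly 15.5 − (4 + 4) = 7.5 lpm unsuctioned, but the suction flows are approximate and the bench concentrations were measured with the same apparatus.

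One might also fault the plan for not sampling at the opening. The protocol does not say that staff work there, and 30 cm is a defensible choice for room exposure.

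**Conclusion.** The point holds in this form: hypothesis 9 judges a safety indicator by statistical significance against an arm with no NO source, with no margin or exposure limit, so neither a significant nor a non-significant result would establish acceptable exposure. The structural argument needs no assumed numbers. Its size does: for an assumed rise of 0.05 ppm, the probability of a significant result runs from above 0.99 to about 0.095 over assumed SDs of 0.02 to 0.25 ppm, with zero background and equal SDs. A rise in NO at 30 cm is plausible but not shown, and no rise in NO2 is indicated. The change is worth making before the trial starts because it is nearly free. It does not touch the PaO2 comparison.

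**What to change.** Reword hypothesis 9 as an absolute criterion: during NO-treated periods, including those reached by crossover, the NO and NO2 readings already planned at 30 cm (30 minutes and one hour) stay below an ambient exposure limit that the sponsor states in ppm for each gas.

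Report, for each gas, the maximum reading and the proportion of infants whose readings all stay below the limit, with an exact confidence interval. As a guide to precision, if all of 20 infants were below the limit, the lower end of the exact 95% interval would be 0.025^(1/20) = 0.83. Keep the oxygen-period readings as a background check, without a between-arm p-value.

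Cost: one hypothesis is reworded, the sponsor must state a limit, and one p-value is dropped. No new measurements are needed. An additional reading at the hood opening would be informative, since the bench NO is highest there outside the hood, but it is optional.

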# **2. Background and significance**

2.1 Elevated A-a DO2 gradients and impaired oxygenation in neonates

The A-a DO2 gradient indicates the difference between the partial pressure of oxygen in the alveoli and that in the arterial blood. This is normally about 10 mmHg in adults and 25 mmHg in neonates after the first two hours of life. At birth there is a transition from the fetal circulation to the neonatal circulation, characterized by a rapid drop in pulmonary vascular resistance with the onset of ventilation, accompanied by improvement in oxygenation. The efficiency of gas exchange in the lungs can be indicated by the ratio of ventilation to perfusion (V/Q). Even in the normal newborn, the distribution of ventilation and perfusion is not as optimal as in older infants or children. A large proportion of the pulmonary blood flow is directed to atelectatic or poorly ventilated alveoli or is shunted right to left through the ductus arteriosus (normally open in the first few hours of life) (5). This results in an elevated A-a DO2 and decreased PaO2 for the neonate as compared to the adult. The A-a DO2 may be as high as 35 mm Hg in the first two hours of life, decreasing to 25 mmHg as lung volume and compliance improve (of the A-a DO2 of 25 mm Hg in the neonate, 14 mm Hg are the normal shunt component and 10 mmHg are the distribution component, with a dead space component of 1 mm Hg and a diffusion component of <1 mm Hg). The normal PaO2 in room air is hence > 60 mm Hg by 2 hours of age and > 70 mm Hg by 12-24 hours of age.

#### A high A-a DO2 hence results from V/Q mismatch or from right to left shunting, either intra-pulmonary or intra-cardiac (shunts are extreme cases of V/Q mismatch where V/Q = 0). This can result from either pulmonary disease, such as with meconium aspiration syndrome, or with elevation of pulmonary pressures to systemic or supra-systemic levels, as with sepsis or idiopathic pulmonary hypertension. The hyperoxia test is often used in term and near-term neonates to differentiate between the right to left shunt as in heart disease or PPHN and a ventilation-perfusion mismatch. A neonate with a mild or moderate V/Q mismatch would usually have a PaO2 > 100 mm Hg after exposure for 5 to 10 minutes to 100% oxygen supplied by a hood, due to diffusion of oxygen to poorly ventilated alveoli. Hyperventilation in combination with hyperoxia may help to further differentiate the fixed right to left shunt of heart disease from labile PPHN.

#### Neonates with hypoxemia (PaO2 < 50 mm Hg) or respiratory acidosis while on 100% oxygen at the onset are usually intubated and mechanically ventilated. The A-a DO2 usually is > 600 mm Hg in this situation, and often more than 630 mm Hg, depending on the PaCO2. However, neonates who present with markedly elevated A-a DO2 (> 500 mm Hg) but with adequate oxygenation (PaO2 50-150 mm Hg on FiO2 > 0.95), respiratory effort, and acid-base status often present a dilemma – to intubate and mechanically ventilate or not? These neonates with either a severe V/Q mismatch (intra-pulmonary shunt) or right to left shunts (extra-pulmonary shunt) (frequently both factors are operative to a variable degree) are often maintained on high oxygen concentrations (FiO2 > 0.7) delivered by oxygen hood, in an attempt to maintain adequate oxygenation and possibly accelerate the spontaneous resolution of elevated pulmonary pressures and minimize the risk of hypoxic pulmonary vasoconstriction or V/Q mismatch without resorting to mechanical ventilation. While some of these neonates improve spontaneously, others persist with high A-a DO2 and ultimately require mechanical ventilation and occasionally ECMO. The neonates who deteriorate are often those with worse oxygenation and higher A-a DO2.

2.2 Inhaled nitric oxide in neonates

Since the discovery that NO is the endothelium derived relaxing factor (6), and the observation that inhaled NO can cause selective pulmonary vasodilation in neonates (7,8), it has been hoped that inhaled NO would be the “magic bullet” that would help manage PPHN. The early case series of Roberts et al. (7) and Kinsella et al. (8) in 1992 showed promising effects of inhaled NO in improving oxygenation without causing systemic hypotension or causing methemoglobinemia. Day et al. (9) randomized neonates with oxygenation indices (OI) of 25 to 40 to receive conventional therapy with or without 20 ppm NO, while neonates with OI >40 all received NO. Systemic hemodynamics did not change while blood gases and ductal shunting acutely improved only in those patients treated with NO. Finer et al. (10) evaluated the dose response to inhaled NO in 23 infants. Eleven of 13 infants with documented evidence of PPHN responded with an increase of PaO2 >10 mm Hg or SpO2>10%. No significant difference was noted in the PaO2 or A-a DO2 response to inhaled NO between 5 and 80 ppm. While these initial studies focused on physiologic outcomes, many subsequent single-center and multi-center trials examined the effect of NO on clinical outcomes. Barefield et al. (11) also showed that inhaled NO led to transient improvements in oxygenation. However, in this study, inhaled NO did not reduce the incidence of meeting ECMO criteria. In a larger trial, Wessel et al. (1) randomized 49 mechanically ventilated neonates with proven PPHN to treatment with or without NO. Sustained improvement in oxygenation was seen in the NO group (the median percentage change for PaO2 was +43% in the NO group and –2% in the control group), although this did not result in decreased mortality or use of ECMO. Only one patient with alveolar capillary dysplasia developed methemoglobinemia after 25 hours of treatment with 80 ppm of NO. None of the patients with favorable transient responses later deteriorated to require ECMO support. Roberts et al. (2) in a multicenter study (the Inhaled Nitric Oxide study group) randomized 58 term neonates with severe hypoxemia and PPHN to either a mixture of oxygen with either a control gas (nitrogen) or NO (80 ppm). If a response to NO was seen within 20 minutes, the treatment was considered successful and was continued at lower concentrations. NO doubled PaO2 in 53%, while only 7% of controls improved. ECMO was required in 71% of the control group and only 40% of the NO group (p=0.02). NO did not cause systemic hypotension, methemoglobinemia, or other side effects. The NINOS study group (3) also conducted a larger (n=235) multicenter study of inhaled NO in neonates >34 weeks gestation with an OI>25. In contrast to the previous study, oxygen was used as the control gas rather than nitrogen. The combined outcome of mortality or need for ECMO was lower in the NO group (46% in NO group vs. 64% in control group, p<0.006). The need for ECMO was also lower (NO group 39% vs. control group 54%, p=0.01), with the NO group showing significant improvement in oxygenation without evidence of toxicity. In a recent commentary, Truog (4) analyzed the cumulative total of the neonates in the previous three studies (1-3). While noting that NO decreased the use of ECMO from 54 to 38%, without increasing the length of stay or prolongation of mechanical ventilation, he also noted that 13% of the enrolled infants died despite all available therapy and that 40% of the neonates did not respond to even high doses of 40-80 ppm of NO (4).

The majority of the available literature as briefly described above deals with neonates on mechanical ventilation, since NO has been used so far as a “rescue” therapy for infants not responding to conventional, and in some cases, high frequency ventilation. Kakuya et al. (12) reported on the use of inhaled NO via a nasopharyngeal tube in an infant with a severely hypoplastic lung and end-stage pulmonary hypertension. Clinical improvement was maintained for seven days with 18-22 ppm NO inhalation. Environmental NO levels were less than 0.06 ppm and NO2 < 0.3 ppm throughout the treatment, well within safety margins. The use of a nasopharyngeal NO delivery system without sedation, as an alternative to endotracheal intubation and sedation, was thought to be advantageous and a practical method in this situation for maintaining a certain quality of life for the patient and family. However, due to entrainment of room air with varying patterns of respiration and varying contributions from mouth breathing, the actual delivered NO level by this method cannot be ascertained with accuracy. The other problem with this method is that the presence of a nasal catheter will partially or even completely occlude one nostril and increase airway resistance significantly (possibly by up to 50%) (13,14), further compromising respiratory effort and oxygenation in a neonate with abnormal gas exchange. NO has also been delivered by a pulsed nasal cannula in older infants and children and shown to decrease pulmonary arterial pressures and resistance as effectively as NO delivered by face mask (15). However, this method has the same flaws as delivery with a nasopharyngeal cannula (12).

